### Data management and quality assurance

To protect confidentiality, the study assigns each participant a unique study identification code (ID). This ID is the only link between the behavioral and biological data and the identifying information collected for locating participants for their follow-up interviews. Locator information is stored separately from other data in a double-locked file cabinet in a locked room with restricted access. Data collection for this study is conducted by highly trained, local implementing staff that develop a rapport with the study participants to engender trust and elicit the most accurate data possible. Data are transmitted each day from the field site to secure servers in the United States. The US-based data manager reviews additional automated quality control checks that the software generates each day. If any critical inconsistencies are noted, the data manager contacts the field project manager who works with the field staff members to resolve the inconsistencies. The principal investigator, other members of the research team, and the field staff also receive daily activity reports.

### Adverse events and severe adverse events

Adverse events (AEs) or severe adverse events (SAEs) related to data collection or any other research activities are reported to the principal investigator and co-investigators within 24 h, and the funding agency and the Institutional Review Board within 48 h, with appropriate action taken immediately. HTC/healthcare clinics and substance use rehab centers follow their standard procedures, including distressed respondent procedures, for any AEs related to the participants that they treat. The study does not interfere with the clinics’ standard operating procedures.

### Evaluation of outcomes

#### Clinic operations and implementation indicators

Prior to the initiation of each cycle, the master trainer from Kheth’Impilo trains the clinic staff on implementation of the WHC program for 2 weeks prior to implementation launch. Clinic staff involved with the WHC receive intensive, manual-supported training on the WHC and must role-play and rehearse the protocol. Following training, the trainer provides ongoing monitoring, coaching, and mentorship for the 6-month follow-up period. The implementing research staff receive training on data collection and methods; clinical manifestations of drug abuse and HIV; issues surrounding confidentiality, especially within the communities where there is concern about local gossip as reported from the formative activities; to ensure that participants are not intoxicated; and to address any HIV-related concerns during research activities [32].

During each cycle and between cycles, we will quantitatively and qualitatively assess barriers and facilitators to the WHC implementation at the clinic level from the perspectives of interventionists, administrators, and other healthcare providers involved in the WHC program. Modifications identified through the cyclical assessments are incorporated into the training of trainers' materials to support continued adaptation and refinements for long-term sustainability. To assess costs, clinic staff interventionists will record the number of minutes spent on various WHC-related tasks, such as preparation, conducting intervention sessions, and referrals.

To measure the implementation processes and outcomes, we will undertake quantitative data collection with providers and review implementation records to assess fidelity of program implementation. Fidelity checks on a random basis will be conducted on the actual groups conducted. Clinic interventionists and other clinic staff who interact with patients participate in the pre-, mid-, and post-implementation FGDs and also complete the self-administered pre- and post-clinic surveys. We will assess seven implementation outcomes to determine program success, as proposed by Proctor and colleagues [13]. Not all implementation outcomes will be assessed across each of the four cycles; however, the protocol for measuring implementation outcomes will remain constant at each cycle. Some of the intervention outcomes will be measured quantitatively and others will be measured qualitatively. The standard implementation outcomes and their measurement methods are outlined in Table 1.

**Table 1 Tab1:** Standard implementation outcomes and their measurement methods

Implementation outcome	Description	Measurement	Data source	Time point
Appropriateness	The extent to which the WHC^a^ is congruent with the culture of the clinic setting	Focus group discussions	Clinic staff, community women, administrators	Formative
	Organizational Readiness	Texas Christian University organizational readiness for change [46]	Interventionists and administrators	Pre-implementation
	Comprehensive Services Linkage Referrals	Self-report	Participants of the WHC	6-month follow-up
	Comprehensive Services Linkage Referrals	Research staff report	Clinic and research staff	Daily
Acceptability	Feedback on the modified WHC	Focus group discussions	Clinic staff and administrators	Multiple time points from mid- to post-implementation
	Client satisfaction	The Client Satisfaction Questionnaire (CSQ-8) [47]	Participants of the WHC	6-month follow-up
Adoption	Current state of implementation of the WHC and challenges to implementing the WHC	Focus group discussions	Clinic staff	Mid- and post-implementation
Cost	Costs associated with implementing the WHC	Clinic-Patient Contact form [48]	Clinic staff	Throughout the implementation cycle
Feasibility	Exposure to and retention of the WHC	Number of WHC modules being delivered	Clinic staff	Throughout the implementation cycle
	Coordination of services related to WHC (e.g., ART)	Percentage of women who are referred to and seek out related services	Participants of the WHC	6-month follow-up
Fidelity	The extent to which interventionists are conducting the WHC as intended	Observer rating forms	Research staff	Weekly
Sustainability	The extent to which the WHC is being implemented as a standard of practice	Self-administered survey	Clinic staff	Every 6 months after exit from clinic until end of study

^a^WHC = Women’s Health CoOp

### Modifications to protocol

The team has made modifications to the protocol to strengthen the study design and facilitate implementation. Table 2 summarizes these changes, which were all approved by the appropriate ethical boards.

**Table 2 Tab2:** Modifications to the protocol and intervention adjustments/considerations

Date	Amendment
August 2015	Required a digital photo-capturing method to document drug and pregnancy tests, to be later verified by the project manager
November 2015	Adopted the use of clinic-issued ARV cards and ARV medication as proof of participant’s HIV-positive status in the absence of patient records
November 2015	Allowed the use of outreach assistants (who are different from the outreach field staff) to identify locations to reach potential participants.
August 2016	Added collecting HIV viral load tests results from participant clinics to validate self-reported ART adherence
August 2016	Added a sustainability questionnaire to be administered to clinic staff, to monitor sustainability of the WHC Intervention Adjustments/Considerations: The drugs of abuse needed some adjustments for the local context from other regions; personalized plan used in previous studies was not found to be feasible because of concerns about time limitations; there was not time for case-management or interventionist follow-up from the sessions; transportation and childcare would have to be considered; training clerks and community healthcare workers such as nurses/clinicians were too busy; fidelity checks cannot always be audio-recorded because of steady intercom usage.

### Power

We used the Stata command, *steppedwedge* [36], which is based on the equation developed by Hussey and Hughes [37] to calculate the detectable difference between participants’ adherence before and after their exposure to the intervention, given a sample size that is feasible and realistic in these clinic settings (*n* = 480; or 120 participants per cluster). We conducted two analyses based on the following parameters: 120 participants per cluster, 240 observations per cluster, and power of .80. The first analysis was used to calculate the detectable difference between participants’ self-reported percentage of ART adherence during the past month before and after the intervention. No previous research has estimated the percentage of ART adherence among South African women who use substances since the government approved the provision of ART to all people living with HIV, regardless of CD4 count. Consequently, we based our analyses on a national estimate of the average percentage of ART adherence in South Africa since the ART rollout (87%; SD = 17.28). Based on this estimate, we will be able to detect an increase or decrease in adherence of 4% or greater. Next, we calculated the detectable difference between the proportion of adherent (i.e., report 95% or greater adherence or are virally suppressed) participants before and after their exposure to the intervention. We based this calculation on previous research that has reported on the proportion of people who engage in substance use that are adherent to ART (56%) [38] and national estimates indicating that 55% of all people living with HIV are virally suppressed [39]. In regards to self-report adherence, we estimate that we will be able to detect a difference of 13% or greater. Similarly, we also estimate that we will be able to detect a difference of 13% or greater to examine the change in the proportion of women who are virally suppressed before and after the intervention.

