### Setting

The WHC is being rolled-out sequentially in four HTC/healthcare clinics and four outpatient substance use rehab centers located in selected disadvantaged communities (townships) in Cape Town. These sites were identified and approved by the City of Cape Town Health Department. Each HTC/healthcare clinic was paired with a substance use rehab center based on geographic proximity, and each pair was randomized by computer into four succeeding 6-month implementation cycles where implementation of the WHC is taking place simultaneously at the paired sites.

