HIV testing is not part of the research because it is performed by clinic staff as part of standard clinic operations. As proof of HIV-positive status, participants must provide a clinic-issued document such as an antiretroviral (ARV) card or ARV medication with identifiable data linking to the participant, or they must consent the research staff to access their hospital records for their results. Viral load is also collected at baseline and 6-month follow-up from the South African National Health Laboratory Service (NHLS) database in the clinics. Viral load testing is also part of the standard of care and the clinics routinely perform HIV viral load testing 6 months after a patient begins taking ART and then 12 months later; however, these intervals may vary by clinic. Viral load test information will be used to validate self-reported ART adherence.

In each cycle, the objective is to enroll 120 women (60 from a HTC/healthcare clinic and 60 from a substance use rehab center) for a sample total of 480, and to follow each enrolled participant at 6 months, with an expected follow-up rate of 90%. At the end of the 6-month follow-up period, we will assess effectiveness of the program using pre-post comparisons to determine whether women reduced their AOD use, are adhering to their ARV regimen, have reduced their sex risk behaviors (e.g., using a condom at every sex act; less transactional sex), and have experienced less to GBV. At the end of each cycle, we will conduct FGDs with a subsample of women who participated in both workshops of the intervention and completed their 6-month follow-up appointment. These study activities will enhance our understanding of women’s satisfaction with the WHC program and suggest modifications to the program for broader acceptability and implementation that will be incorporated into the next cycle.

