### Analysis

The analysis will treat count outcomes as Poisson distributed. A number of multilevel factors can impact the outcomes, including site/clinics, city, time, and the type of the site (HTC vs. substance use rehab). Because individuals are clustered within sites and sites are clustered within a city, we need to consider the variance inflation factor that results in this clustering. We considered a number of approaches: using random effects, fixed effects, or Generalized Estimating Equations (GEE) considering population-averaged methods. Although a random effects model for sites seems a natural approach, we needed to consider fixed effects of the city and of the site type, which would leave little power left to estimate the random effects distribution. Consequently, we will also use two other methods, GEE and the fixed effects model, to assess sensitivity by comparing the results across these models.

We will use Stata Release 14 (College Station, TX) and SAS version 9.2 (Cary, NC). Data will be examined to determine the extent to which they meet appropriate distributional assumptions. We will use methods described by Ecob and Der to identify outliers in longitudinal models and use methods of case downweighting when extreme cases are identified [40]. Missing data will be handled using multiple imputation methods [41]. The patient-level analyses will be organized into three groups to examine (a) successful reduction of risk behaviors targeted by the WHC (i.e., effectiveness), (b) patient satisfaction, and (c) increasing the number of women receiving ART and adhering to ART, and being admitted to substance use rehab.

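### The detectable differences of 4 and 13 points come from a stepped-wedge formula that does not describe the patient data collected, assume no loss to follow-up, and state no intracluster correlation

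*Protocol article*

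**What the plan says.** The Power section of the protocol article describes the target as the difference in participants' adherence before and after exposure. It computes this with a Stata stepped-wedge command "which is based on the equation developed by Hussey and Hughes". The inputs listed are "120 participants per cluster, 240 observations per cluster, and power of .80", for a total of "480; or 120 participants per cluster". For mean adherence (87%, SD 17.28) it concludes that "we will be able to detect an increase or decrease in adherence of 4% or greater". For the proportion adherent (56%) or virally suppressed (55%) it gives 13% or greater. It does not state alpha, the number of periods or an ICC.

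Elsewhere the article describes the data as follows:

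- Setting: four clinic/rehab pairs, where "each pair was randomized by computer into four succeeding 6-month implementation cycles".
- Patient-level process and data collection: each woman has a baseline and a 6-month visit, "with an expected follow-up rate of 90" per cent, and effectiveness is judged by pre-post comparison.
- Analysis: change from baseline to 6 months, with paired t-tests followed by multivariable models. On clustering it says "we need to consider the variance inflation factor that results in this clustering".

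**The concern.** The Hussey-Hughes variance belongs to a layout in which each cluster contributes separate observations in every period, some before and some after it crosses over. The patient-level study has no such layout. No patient outcome is described for a pair before its own cycle or after its women's 6-month visit; the later sustainability checks are completed at clinic level. The 240 observations are the same 120 women seen twice, and the formula has no term for within-woman correlation.

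The printed figures are therefore the power neither of the pre-post comparison nor of a time-adjusted analysis of the data collected. This matters because the Study design section credits the design with accounting for temporal trends such as universal ART coverage. A null adherence result would be read against thresholds that belong to neither analysis.

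**Working it through.** **Inputs from the article.** 480/120 = 4 clusters; 240 observations per cluster; power 0.80; SD 17.28; baseline proportion 0.56, so SD = 100 × √(0.56 × 0.44) = 49.64 points; follow-up 90%.

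**Assumed, because not stated.** Two-sided alpha 0.05; 5 periods (one before any cluster crosses over, then four steps), so 240/5 = 48 observations per cluster-period; ICC varied.

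**1. Reproducing the stated figures.** With I = 4 clusters, T = 5 periods, U = 10, W = 30, V = 30, cell variance s² = SD²(1 − ICC)/m and between-cluster variance t² = SD² × ICC:

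Var = I s²(s² + T t²) / [(IU − W)s² + (U² + ITU − TW − IV)t²]

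The bracket is 10s² + 30t². The detectable difference is 2.80 × √Var.

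At ICC 0, Var = 0.4s².

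- Mean: s² = 17.28²/48 = 6.221; Var = 2.488; SE = 1.577; difference = **4.42 points**.
- Proportion: s² = 2464/48 = 51.33; Var = 20.53; SE = 4.531; difference = **12.7 points**.

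These round to 4 and 13. At exactly 4 points, 4/1.577 − 1.96 = 0.58, so power is about **72%**, not 80%.

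**2. Same formula, non-zero ICC and 90% follow-up.** Observations per cluster become 120 + 108 = 228, or 45.6 per cluster-period.

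| ICC | 240 obs: mean / proportion | 228 obs: mean / proportion |
|---|---|---|
| 0 | 4.42 / 12.7 | 4.53 / 13.0 |
| 0.01 | 5.19 / 14.9 | 5.31 / 15.3 |
| 0.05 | 5.43 / 15.6 | 5.56 / 16.0 |
| 0.10 | 5.35 / 15.4 | 5.48 / 15.8 |

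Worked cell (ICC 0.05, 240 observations): s² = 5.910, t² = 14.93; Var = 4 × 5.910 × (5.910 + 74.65)/(59.10 + 447.9) = 3.756; 2.80 × 1.938 = 5.43.

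The function is not monotone in the ICC. It peaks near 0.05 and falls again, so an ICC of about 0.4 also gives 4.41 and 12.7.

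**3. Plain pre-post contrast.** Completers: 0.90 × 480 = 432. Assumed within-woman correlation 0.5; no between-site variation in change; no control for time.

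- Mean: 2.80 × 17.28 × √(2 × 0.5/432) = **2.3 points**.
- Proportion: 2.80 × 49.64 × √(1/432) = **6.7 points**.

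**4. Time-adjusted analysis of the data collected.** Generalised least squares on two cells per pair (120 women, then 108), with period effects and a random cluster effect. Each pair's follow-up is assumed to share a period with the next pair's baseline.

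| ICC | Within-woman correlation 0.5 | Within-woman correlation 0 |
|---|---|---|
| 0.01 | 3.7 / 10.7 | 4.3 / 12.3 |
| 0.02 | 4.3 / 12.4 | 4.8 / 13.8 |
| 0.05 | 5.7 / 16.3 | 6.1 / 17.4 |
| 0.10 | 7.4 / 21.4 | 7.7 / 22.2 |

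If follow-ups and the next baselines do not overlap in calendar time, this effect cannot be estimated. The article describes lessons-learned periods between cycles, so overlap is not assured.

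**The case against.** Four points can be made for the plan.

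- **The two figures agree.** A reader might infer that 4 and 13 contradict each other, since 4/17.28 = 0.231 SD and 13/49.64 = 0.262 SD. That does not stand. Whole-number rounding allows 0.203 to 0.260 and 0.252 to 0.272, which overlap, and one calculation yields 4.42 and 12.7. What remains is that 4.4 was rounded down.
- **Clustering may not have been ignored.** A reader might infer that the authors set the ICC to zero. The article does not show this. Alpha, periods and ICC are unstated; an ICC near 0.4 also matches, as do some other layouts and one-sided alpha in narrow windows. A condensed article may also leave the ICC to the full protocol. The objection stands as far as intent goes. It does not rescue the figures: at two-sided 0.05, no layout tried gave both for ICCs of 0.01 to 0.10.
- **Loss to follow-up matters little.** At ICC 0 it moves the figures only from 4.42 / 12.7 to 4.53 / 13.0, and multiple imputation is planned. The effect is indeed small. Imputation keeps these women in the analysis but does not make 240 observed values.
- **The stated figures may be conservative.** For the uncontrolled paired contrast they are, before any between-site variation in change. This stands, and it rules out a blanket claim that the trial is underpowered.

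**Conclusion.** The point holds as a mismatch between the power statement and the trial. The formula needs data that the patient-level study does not collect, the 240 observations contradict the planned 90% follow-up, and the listed inputs omit the ICC although the Analysis section says clustering must be considered.

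Within the formula, the stated pair is recovered after rounding at ICC 0 or at an implausibly large ICC of about 0.4. At ICCs of 0.01 to 0.10 with 228 observations it becomes 5.3 to 5.6 and 15.3 to 16.0 points. These values show how sensitive the calculation is; they are not replacements, because they come from the same unsuitable formula and from assumed ICCs.

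The tempting conclusion that the trial lacks its stated power is not supported in general. The true detectable difference is smaller than stated for a plain pre-post contrast (about 2.3 and 6.7 points) and larger for a time-adjusted analysis once the ICC exceeds roughly 0.02. All of this rests on two-sided 0.05, 5 periods, the stated SDs, and an assumed within-woman correlation of 0.5 unless shown otherwise.

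**What to change.** Replace the detectable differences in the Power section with figures for the analysis that will be run: change from baseline to 6 months in about 432 completers. State alpha, the within-woman correlation and the between-site variation in change, and show results over a range of the last two. If a time-adjusted effect is intended, give its detectable difference separately, with the ICC range and the assumed calendar overlap between cycles. Report values to one decimal, not rounded down, and do not present the Hussey-Hughes figures as this trial's power.

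The cost is a recalculation and a rewritten paragraph. The sample size was set by what is feasible in these clinics, so enrolment is unaffected.

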### Analysis

The analysis will treat count outcomes as Poisson distributed. A number of multilevel factors can impact the outcomes, including site/clinics, city, time, and the type of the site (HTC vs. substance use rehab). Because individuals are clustered within sites and sites are clustered within a city, we need to consider the variance inflation factor that results in this clustering. We considered a number of approaches: using random effects, fixed effects, or Generalized Estimating Equations (GEE) considering population-averaged methods. Although a random effects model for sites seems a natural approach, we needed to consider fixed effects of the city and of the site type, which would leave little power left to estimate the random effects distribution. Consequently, we will also use two other methods, GEE and the fixed effects model, to assess sensitivity by comparing the results across these models.

We will use Stata Release 14 (College Station, TX) and SAS version 9.2 (Cary, NC). Data will be examined to determine the extent to which they meet appropriate distributional assumptions. We will use methods described by Ecob and Der to identify outliers in longitudinal models and use methods of case downweighting when extreme cases are identified [40]. Missing data will be handled using multiple imputation methods [41]. The patient-level analyses will be organized into three groups to examine (a) successful reduction of risk behaviors targeted by the WHC (i.e., effectiveness), (b) patient satisfaction, and (c) increasing the number of women receiving ART and adhering to ART, and being admitted to substance use rehab.

To assess effectiveness, the analysis will compare changes from baseline to 6-month follow-up on the amount of alcohol consumption, biological and self-reported drug use, condom use at last sex, number of sex partners over the past 6 months, and values from scales that measure relationship power and communication. We will start with descriptive analyses, including measures of central tendency, and dispersion (e.g., means, medians, proportions, standard deviations). Bivariate analysis will include paired t-tests, Wilcoxon rank-sum, and tabular statistics and the chi-square test. For multivariable analysis, the xtlogit and xtgee function will be used to specify random effects or fixed effects, and will assume that the correlation matrix is exchangeable. The models will control for other covariates identified in bivariate analyses or hypothesized a priori (e.g., condom use is correlated with substance use). One of the most important covariates in the model will be measures of patient satisfaction. Model performance and fit will be assessed with incremental elimination of variables, likelihood ratio tests, and changes in the Akaike information criterion (AIC) and Bayesian information criterion (BIC) values.

Patient satisfaction analyses will be predominately descriptive to determine if satisfaction improves with each cycle, varies by type of clinic, and by participant characteristics (e.g., alcohol use, pregnancy status).

We assume that the prevalence of patients receiving or adhering to ART or receiving treatment for substance abuse are Poisson distributed and increase from baseline to follow-up. We will use a similar approach outlined in the effectiveness analysis for bivariate and multivariable analyses. Variables considered for multivariable analysis will include patient characteristics, measures of patient success with the WHC, patient satisfaction, and clinic-level characteristics (e.g., type of clinic, provider satisfaction).

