### Patient-level process and data collection

The patient-level study includes a baseline visit and a 6-month follow-up visit to evaluate intervention effectiveness. Eligibility criteria include (1) being between the ages of 18 and 45 years, (2) self-reporting use of at least one drug, including alcohol, at least weekly during the previous 3 months, (3) reporting unprotected sex with a male partner in the past 6 months, (4) having a positive verifiable HIV test result, (5) reporting the intention to remain in the area for at least the next 6 months, (6) providing contact information, and (7) being willing to participate in alcohol and other drug screening.

A field team hired by Kheth’Impilo, the local nongovernmental implementing partner, leads the outreach and data collection activities. Trained outreach workers operate as recruiters of women within clinics and surrounding communities and track eligible women for the study, while data capturers collect patient-level data from participants at the baseline and 6-month follow-up appointments. These are well-established methods from other studies conducted in the region [34, 35]. Once participants are enrolled, clinic staff trained and certified in the WHC offer the adapted intervention to all women enrolled and to other women in their clinics who may be interested in participating, so as to operate as a real-world setting.

At each data collection visit, a member of the research/implementing team administers a face-to-face interview using a secure tablet with skip patterns and quality-control checks programmed into the interview. The study instrument includes measures of socioeconomic status, sex risk behaviors, AOD use, substance abuse treatment readiness, ART use and barriers to use, and other self-reported clinical outcomes such as TB and symptoms for sexually transmitted infections. Biological data are obtained from a urine specimen tested for pregnancy and metabolites for recent drug use. Participants also undergo a breathalyzer test for recent alcohol use. The same measures are collected at 6-month follow-up.

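### The clustering plan uses a city effect that cannot exist and omits visits within woman, and its one-grouping commands leave the standard error of the pre-post effect unsecured

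*Protocol article*

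**What the plan says.** The Setting section describes "four HTC/healthcare clinics and four outpatient substance use rehab centers located in selected disadvantaged communities (townships) in Cape Town", and says that "each pair was randomized by computer into four succeeding 6-month implementation cycles". Under Patient-level process and data collection, "The patient-level study includes a baseline visit and a 6-month follow-up visit to evaluate intervention effectiveness", and each cycle aims to "enroll 120 women (60 from a HTC/healthcare clinic and 60 from a substance use rehab center) for a sample total of 480". Effectiveness is judged by the change from baseline to 6 months.

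The Analysis section describes individuals nested in sites and sites nested in a city. It calls random site effects the natural approach, then says "we needed to consider fixed effects of the city and of the site type, which would leave little power left" for estimating the random-effects distribution. It concludes that "we will also use two other methods, GEE and the fixed effects model, to assess sensitivity" by comparing results across the models. For multivariable work, "the xtlogit and xtgee function will be used to specify random effects or fixed effects, and will assume that the correlation matrix is exchangeable". Model fit is to be judged by likelihood-ratio tests, AIC and BIC.

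**The concern.** Three things in the stated plan do not fit the design.

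- **City.** A level with one member has no effect to estimate, yet it is half of the reason given for doubting random effects.
- **Missing level.** The data are visits within women within sites. The clustering statement starts at the individual and leaves out the repeated visit, on which the pre-post effect rests.
- **Commands.** xtlogit and xtgee each carry one grouping variable. A single exchangeable correlation can represent visits within a woman or observations within a site, but not both.

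The width of the interval for the pre-post effect then depends on which grouping is chosen and on how much change differs between sites. GEE is also a weak answer to a random-effects distribution that is hard to estimate: with 8 sites or 4 randomised pairs, its usual robust variance has the same shortage of clusters. At stake are false-positive claims of effectiveness, or lost precision, and a model comparison that could reassure for the wrong reason.

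**Working it through.** **Inputs from the article.** 8 sites in 4 randomised pairs; 60 women per site; 90% follow-up expected, so 60 × 0.9 = 54 completers per site and 8 × 54 = 432 in total; 2 visits per woman; adherence SD 17.28.

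**Assumptions, because the article gives no values.** Within-woman correlation ρ = 0.5 (0.3 to 0.7 in the simulation); ICC of the within-woman change between sites of 0 to 0.05; two-sided α = 0.05. That the commands take one grouping variable is general knowledge of the software.

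**The plan's own figures.** The Power section gives detectable differences of 4 and 13 points. The stepped-wedge variance formula it cites, with 4 clusters, an assumed 5 periods, 240/5 = 48 observations per cluster-period and ICC 0, gives 4.42 and 12.7 points, which round to those values. This point disputes neither figure.

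**1. City.** For eight sites, a design with intercept, city and site type has rank 2 out of 3 columns. City duplicates the intercept, drops out and uses no degrees of freedom.

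**2. Grouping by woman.** A stable site effect cancels in the within-woman change; a site difference in change does not. The variance is then understated by the design effect DE = 1 + (54 − 1) × ICC, and the actual type I error is 2 × [1 − Φ(1.96/√DE)].

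| ICC of change | DE | Type I error |
|---|---|---|
| 0 | 1.00 | 5% |
| 0.01 | 1.53 | 11% |
| 0.02 | 2.06 | 17% |
| 0.05 | 3.65 | 30% |

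**3. Grouping by site, exchangeable, model-based SE.** A woman's two visits are treated like visits of two different women. Relative to the correct paired SE, the model SE is 1/√(1 − ρ) = 1/√0.5 = 1.41. The true SE is √DE times the paired SE, so the ratio of model SE to true SE is 1.41/√DE:

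- ICC of change 0: 1.41, too wide.
- ICC of change 0.02: 1.414/1.435 = 0.985, about right.
- ICC of change 0.05: 1.414/1.910 = 0.74, too narrow; type I error 2 × [1 − Φ(1.96 × 0.74)] = 15%.

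**4. Grouping by site, sandwich variance, normal reference (not stated in the article).** With K equal clusters, the uncorrected sandwich SE is √((K − 1)/K) times the usual SE of the mean of K cluster changes. The test therefore rejects when |t| on K − 1 df exceeds 1.96 × √((K − 1)/K). With the factor K/(K − 1) restored but a normal reference kept, the cut-off is 1.96.

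- K = 8: P(|t₇| > 1.83) = 10.9%; P(|t₇| > 1.96) = 9.1%.
- K = 4: P(|t₃| > 1.70) = 18.8%; P(|t₃| > 1.96) = 14.5%.

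**5. Check by simulation.** 4,000 runs per setting, 8 sites × 54 completers, SD 17.28, ρ = 0.5, site ICC 0.05. The first column is the share of site variance specific to the visit period; the last three are type I error.

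| Period-specific share | True SE | SE by site | SE by woman | By site | By woman | Uncorrected sandwich |
|---|---|---|---|---|---|---|
| 0% | 0.82 | 1.14 | 0.81 | 0.6% | 5.3% | 11.4% |
| 20% | 1.18 | 1.15 | 0.82 | 5.6% | 17.4% | 10.4% |
| 50% | 1.57 | 1.15 | 0.83 | 14.7% | 30.2% | 10.5% |

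The 20% and 50% rows correspond to an ICC of change of 2 × 0.01/(2 × 0.01 + 0.95) = 0.021 and 2 × 0.025/(2 × 0.025 + 0.95) = 0.05, so they agree with steps 2 and 3. With 4 pairs the uncorrected sandwich gave 19.1%. With the small-sample factor and a t reference, type I error was 4.8 to 5.6% in all settings run.

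**The case against.** A reader might infer that the error bars for the pre-post effect are wrong. The article does not support that. It states neither the grouping variable, nor the variance estimator, nor how much change varies between sites. Grouping by woman is correct if change is the same at every site, and grouping by site is about right at an ICC of change of 0.02. The two cannot both be wrong by the largest amounts shown, because those need opposite conditions. If one model came out wide and another narrow, comparing them might reveal it.

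A reader might also infer that the plan moves to GEE because clusters are few. It does not say so. Random effects stay in the plan, GEE and fixed effects are added as sensitivity checks, and the reason given is the city and site-type effects.

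Other parts of the defence also have weight. The article refers to repeated measures at patient level and to paired t-tests, so the pairing is known to the authors. Woman as panel with site indicators would cover stable site differences, and would absorb pair main effects too. SAS is also named, so the two commands may not be the whole plan. Likelihood-ratio tests, AIC and BIC are not tied to xtgee, and they are valid for likelihood-based fits. The choice of grouping variable and variance estimator is commonly left to an analysis plan, so its absence from an article is not itself a fault.

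This limits the claim but does not remove it. The city rationale and the clustering hierarchy are stated, and they do not match the design. The commands and correlation structure are also stated, and no choice of one grouping variable lets change vary between sites while keeping the pairing within women. Some such variation is likely here: the programme is modified after each cycle, each pair has its own calendar period, site staff deliver it, and clinics differ in kind from rehab centers. An ICC of change of 0.01 is enough for 11%.

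**Conclusion.** The point holds in limited form. Firmly established from the text: the city effect contradicts the setting and supports no argument about random effects; the clustering statement omits visits within woman; and the named one-grouping commands cannot carry both levels.

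What follows is that the standard error is not secured, in either direction. Under the stated assumptions, type I error for woman grouping runs from 5% to about 30%. For site grouping with model-based standard errors, the SE runs from 1.41 times too large to 0.74 of its true value. The sandwich figures, about 9 to 11% with 8 sites and 14 to 19% with 4 pairs, are a risk that applies only if that variance is used with a normal reference. The within-woman correlation and the ICC of change are assumed throughout, so no single corrected figure exists. The point should be acted on before analysis.

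**What to change.** - Delete the city effect and the rationale that rests on it.
- State the hierarchy as visits within women within sites, with sites in four randomised pairs.
- Main model: a mixed model with a woman random intercept, site effects and between-site variation in the visit effect, tested with small-sample inference (t on 7 df for 8 sites). With equal site sizes and a continuous outcome, this amounts to a t-test on the eight site mean changes. Repeat on the four pair changes (3 df) as a check.
- Do not also enter pair as a main effect when sites are fixed, since each site belongs to one pair.
- Keep GEE only with a small-sample variance correction and a t reference.
- Restrict likelihood-ratio tests, AIC and BIC to likelihood-based fits.

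The cost is analysis wording and code; no data collection changes. The critical value rises from 1.96 to 2.36, so for a given standard error the interval is 2.36/1.96 = 1.20 times as wide, and it may widen further if change does vary between sites. The 3-df check will have low power and should be read as a check only.
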